## Abstract

**Background:**

Despite a number of clinicians having been trained in Parent–Child Interaction Therapy (PCIT) in Aotearoa/New Zealand, few are regularly delivering the treatment, with barriers to use including a lack of suitable equipment and lack of professional support. This pragmatic, parallel-arm, randomised, controlled pilot trial includes PCIT-trained clinicians who are not delivering, or only rarely utilising, this effective treatment. The study aims to assess the feasibility, acceptability and cultural responsivity of study methods and intervention components and to collect variance data on the proposed future primary outcome variable, in preparation for a future, larger trial.

**Methods:**

The trial will compare a novel ‘re-implementation’ intervention with a refresher training and problem-solving control. Intervention components have been systematically developed to address barriers and facilitators to clinician use of PCIT using implementation theory, and a draft logic model with hypothesised mechanisms of action, derived from a series of preliminary studies. The intervention includes complimentary access to necessary equipment for PCIT implementation (audio-visual equipment, a ‘pop-up’ time-out space, toys), a mobile senior PCIT co-worker and an optional weekly PCIT consultation group, for a 6-month period. Outcomes will include the feasibility of recruitment and trial procedures; acceptability of the intervention package and data collection methods to clinicians; and clinician adoption of PCIT.

**Discussion:**

Relatively little research attention has been directed at interventions to resurrect stalled implementation efforts. Results from this pragmatic pilot RCT will refine and shape knowledge relating to what it might take to embed the ongoing delivery of PCIT in community settings, providing more children and families with access to this effective treatment.

**Trial registration:**

ANZCTR, ACTRN12622001022752, registered on July 21, 2022.

**Supplementary Information:**

The online version contains supplementary material available at 10.1186/s40814-023-01309-y.

## Contributions to the literature

Implementation efforts in real-world settings often involve training cohorts of clinicians in an EBT and hoping they will use it in their work—an approach that typically has limited success.There are seldom efforts to ‘re-implement’ or resurrect a stalled implementation initiative with trained clinicians who are not (or are only rarely) using the EBT, even where clinicians view the EBT as effective and acceptable.This randomised, controlled, pilot study will assess the feasibility, acceptability and cultural responsivity of a new Parent–Child Interaction Therapy (PCIT) re-implementation intervention. It compares refresher training and a package of re-implementation supports (with each component selected deliberately to address identified barriers) with refresher training alone.

## Background

A degree of challenging behaviour such as defiance, non-compliance or aggression is developmentally normal in childhood. However, for a proportion of children, these difficulties are sustained beyond early childhood and may become adversely impactful on child wellbeing and family functioning. Clinical-level childhood conduct problems are among the most common mental disorders formally diagnosed in children under 7 years internationally, represent around half of all childhood psychopathology, are one of the most common reasons for children to be referred to mental health services and were the leading cause of burden (within all mental disorders) for 0–14-year-old children in the most recent Global Burden of Disease study [1–4]. Indigenous children are often over-represented in prevalence data, with complex factors, including the experience of colonisation, racism and subsequent socioeconomic adversity, likely to be relevant. This has been described in relation to Indigenous Māori tamariki (children) and whānau (families) in Aotearoa/New Zealand (see [5–7]).

Evidence-based treatments for childhood conduct problems typically involve ‘parent training’ approaches, based on social learning theory and attachment principles [2]. Parent–Child Interaction Therapy (PCIT; [8]) is one example and is somewhat distinctive from other programmes in its use of in vivo (live) clinician coaching of parents with their 2.5 to 7-year-old children, typically utilising a one-way mirror and a discrete ear-piece for the parent for approximately 12–20 weekly sessions [8]. Meta-analyses have shown that PCIT is effective in reducing conduct problems in children, improving child compliance, reducing parent stress and improving parent emotion regulation and reflective functioning [9–12]. There is mixed evidence relating to PCIT’s effectiveness with indigenous populations [13].

### Implementation of PCIT in Aotearoa/New Zealand

To become accredited in PCIT with PCIT International (www.PCIT.org), a registered masters-level clinician (e.g. psychologist, psychiatrist, social worker, therapist) must initially undertake a 40-h training in the approach, followed by fortnightly PCIT consultation and observation of practice until at least two PCIT cases have been completed successfully. In Aotearoa/New Zealand, approximately 135 clinicians have participated in the 40-h PCIT training since its introduction to the country in 2010 ([name], personal communication, May 2022) and 13 (i.e. 9.6%) are accredited as PCIT therapists with PCIT International (www.pcit.org; accessed 6 May 2022), this excludes the national trainer and two within-agency trainers.

Existing research suggests that PCIT is viewed as an effective and acceptable intervention to both PCIT-trained clinicians in Aotearoa/New Zealand [14, 15], to Indigenous Māori parents when delivered ‘by Māori, for Māori’ [13], and to families accessing a public mental health service in Aotearoa/New Zealand [16]. However, a 2019 survey of PCIT-trained clinicians in Aotearoa/New Zealand found that—even where the clinician was using PCIT in their work—the average number of families seen per week for PCIT, per clinician was 1.03 [15]. A subsequent 2021 survey of PCIT-trained clinicians found that the median (IQR) typical number of clients seen for PCIT per week was 0 (0 to 1) in Aotearoa/New Zealand, compared to 2 (2 to 3) in Australia, a statistically significant difference [14].

Clearly, despite clinicians having received intensive training in an evidence-based treatment that is acceptable to them, encountering barriers in the real world of service delivery may result in relatively few delivering PCIT to a few families. This research-to-practice gap is a product of complex determinants and is well recognised internationally [17–21].

Implementation science is a relatively new field of research, with a focus on developing knowledge around strategies that are effective for embedding or implementing already-proven treatments into usual care environments [21, 22]. The design of many implementation interventions has historically been driven by the ‘It Seemed Like A Good Idea At The Time’ (ISLAGIATT) principle, and there have been calls for more systematic and theory-driven development of implementation interventions, in order to improve their effectiveness and specificity [23]. The Theoretical Domains Framework of behaviour change is a compilation of domains which condense and describe modifiable factors that may influence clinician behaviour [24]. The 14 domains have been mapped onto three central factors: an individual’s Capability (physical and/or psychological), Opportunity (social and/or physical) and Motivation (automatic and/or reflective) to perform a particular behaviour [24, 25]. This COM-B model can be used to understand influences on clinician behaviour and facilitate the systematic design of implementation interventions [23]. Incorporating models such as the COM-B may also more readily enable the outcomes of these interventions to be linked to mechanisms of action—another important direction for the field [26].

### Proposed intervention

Our recent systematic review of existing interventions to support the implementation of PCIT suggested that PCIT implementation research has been disproportionately targeted at training initiatives [27]. Rather than prioritising the training of more clinicians in PCIT (though this remains important), our intention is to better understand what it would require for already-trained clinicians to begin (or resume) implementing PCIT in their practice. We have described this as ‘re-implementation’, which we defined as ‘resuming implementation, implementing again and/or implementing differently’ [14]. Relatively little research attention has been given to reinvigorating unsuccessful programme implementation, possibly due to pragmatic considerations such as grant funding expiring after initial implementation efforts (i.e. initial training of clinicians). Although there have been recent indications of interest in the area—which has been described as ‘implementation, interrupted’ in Uganda [28].

In our preliminary work, we sought to understand the barriers and facilitators of clinician use of PCIT in Aotearoa/New Zealand, following the systematic method advocated by Atkins [23]. We acknowledge that there will be a proportion of clinicians who do not use PCIT post-training for compelling reasons, such as cessation of clinical practice, or those to whom the approach is not acceptable. Our interest is in those clinicians to whom PCIT is acceptable, who may have encountered barriers which have impeded their initial desire to incorporate PCIT in their practice. Through engaging with PCIT-trained clinicians in surveys and focus groups, we have identified that these barriers include the lack of access to suitable equipment to support the delivery of PCIT (for example, audio-visual equipment) and families being unable to easily attend clinic-based sessions (traditionally held during working hours in a fixed location) [14]. Facilitators of PCIT’s use included access to a suitable room or clinic space, the ability to co-work PCIT cases with another clinician and having other PCIT-trained colleagues in the workplace [14].

The package of re-implementation supports described in this paper has been specifically designed to address these identified barriers and is based on a preliminary logic model of mechanisms of action from our earlier work (paper in preparation). In summary, we hypothesise that the difficulties accessing equipment (physical opportunity) and lack of a co-worker and concerns from colleagues and administrators about components of PCIT (social opportunity) work to decrease motivation to implement PCIT (the behaviour). Introducing a PCIT co-worker and regular group consultation sessions is hypothesised to improve psychological capability and social opportunity, and providing equipment (time-out tents and audio-visual equipment) is hypothesised to increase both physical and social opportunity; both of which influence motivation to implement PCIT (the behaviour). The package of supports is designed to be flexibly utilised, for example outside of traditional clinic hours or in a family’s home, and we anticipate that this will better facilitate client attendance.

Piloting this novel package of supports will allow us to refine the development of the re-implementation intervention [29], and our preliminary logic model, in order to increase the specificity of mechanisms of action to test in a future trial [30].

### Study aims

The primary objective of this pilot study is to assess the feasibility of conducting a RCT. In the future, this fully powered RCT will assess the effects of the provision of a re-implementation intervention on the adoption of PCIT by clinicians who are not—or are rarely—using PCIT in their practice. The current feasibility trial will identify any factors that may detract from our ability to achieve this aim in the full trial.

This trial aims the following:Pilot the recruitment and trial procedures to assess recruitment rates, assess the characteristics of clinicians who enrol in the trial, assess whether the idea of randomisation is acceptable to participants.Identify any specific cultural factors that may influence recruitment, data collection methods or sampling frameworks and determine the acceptability of the reimplementation intervention for Māori participants.Assess the acceptability of the re-implementation package to clinician participants, in order to refine the components of the PCIT re-implementation intervention.Pilot the use of a series of online self-report surveys as a data collection method for assessing the effects of the re-implementation intervention on clinician capability, opportunity and motivation.Explore potential effects of the PCIT re-implementation intervention on clinician adoption of PCIT. This will include identifying the variability of the proposed primary outcome variable at the end of the intervention, to calculate an appropriate sample size for a definitive RCT.

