#### Randomisation and blinding strategies

All participants will have been recruited and will have participated in the two refresher training days (refer ‘Study Treatments’, below) prior to random allocation to intervention and control groups. Allocation to groups will occur at the end of the second day of refresher training. A random allocation sequence will have been generated by the study statistician (using a simple 1:1 randomisation with no restrictions), who will contact participants via email with their group allocation. Participants will be asked not to share the email or reveal or discuss the condition to which they have been allocated. We will undertake a test of blinding at the end of the intervention (i.e. will ask participants which condition they believed themselves to have been allocated) in order to determine whether blinding is feasible in a future trial.

The first author will be delivering some of the re-implementation supports and will therefore be unable to be blinded. The remainder of the research team, particularly outcome assessors, will be blinded.

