### Intervention and control conditions

#### All participants

All participants will undertake a 2-day refresher training, the content of which is informed by PCIT International’s ‘recalibration’ training, by previous research into implementation barriers encountered by clinicians in Aotearoa/New Zealand and culturally responsive practices. This complimentary, catered training will be delivered on two successive Saturdays, to facilitate clinician attendance regardless of their current employment context. It will be co-delivered by an experienced Māori PCIT provider and a senior PCIT trainer in Tāmaki Makaurau/Auckland and will only be delivered virtually if absolutely necessary due to COVID-19 restrictions.

Incorporated within the two training days, *all* participants will receive the following enhanced supports:A collection of resources to support delivery, including detailed virtual delivery resources and demonstration of these. Access to a Dropbox with all resources and materials.A voucher for a complimentary pack of 25 Eyberg Child Behaviour Inventory (ECBI; [33]) questionnaires to use with future PCIT clients, and a complimentary PCIT treatment protocol in the event that this has been misplaced since their initial PCIT training.Facilitated discussion and problem-solving sessions around using PCIT in various contexts including private practice should participants choose to do this. For example, what to charge for PCIT, how to obtain referrals and where suitable clinic rooms are located.Discussion, facilitated by a Māori PCIT provider, relating to how to deliver PCIT in a culturally responsive way.

After the two training days, *all* participants across both groups will be offered optional complimentary weekly 1-h group PCIT-oriented consultation with a senior PCIT clinician, for the 6-month trial period.

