#### Intervention

Specific components of the intervention are provided in Table 1, according to the TIDieR checklist [34]. In summary, clinicians allocated to the intervention condition will receive the following:A pack of suitable PCIT *toys* to use with children and families, which will be provided free of charge.Access to a mobile *co-worker*/‘PCIT partner’ who can be booked through an online booking system free of charge at any time. This senior PCIT clinician will be available to join a client session to support the clinician (the clinician is responsible for obtaining client consent for this to occur), or to plan or debrief sessions, as requested by the clinician, and in any location of the clinician’s choice. We will recruit a senior Māori PCIT clinician to this role, as Māori are the Indigenous people of Aotearoa/New Zealand and a number of PCIT-trained clinicians are Māori (14.8% in our 2021 survey).Access to portable, relocatable *audio-visual equipment,* including a high quality digital remote camera and monitor, which allows viewing of the clinic room from a nearby room and a Bluetooth earpiece to facilitate clinician coaching of the parent(s) from the nearby room.Access to an in-room *time-out pop-up cubicle* to be used if the child requires a brief time-out, that is transportable to the participant clinician’s clinic room of choice.

**Table 1 Tab1:** Re-implementation intervention components, described using the TIDieR checklist

Brief name	Re-implementation support package for PCIT-trained clinicians
Why	PCIT is an effective treatment for childhood conduct problems, and a number of clinicians have received a five-day initial training in the approach since it was introduced to Aotearoa in 2010. Our earlier work suggests that, despite PCIT-trained clinicians viewing PCIT as effective and acceptable, relatively few are using it in their work, and those who are using it, are seeing a small number of families. The majority of PCIT-trained clinicians describe having encountered barriers to its use, which include lacking suitable equipment, and families having difficulty accessing clinic-based sessions. Facilitators of PCIT’s use included access to a suitable clinic room, and the ability to co-work PCIT cases with another clinician. These earlier studies have shaped the selection of intervention components, which have also been informed by the COM-B behaviour change theory

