### Outcomes and measures

Baseline data will be collected from all participants, via a Qualtrics survey prior to allocation being revealed. The re-implementation intervention will be available for a period of 6 months to the intervention group. Some aspects of the re-implementation intervention occur at one point in time (e.g. the refresher training) and others continue across the trial period (e.g. access to equipment and co-worker, consultation). All aspects of the intervention will be contained within a 6-month period and will cease at that point. Table 2 provides a summary of outcomes and measures.

**Table 2 Tab2:** Summary of outcomes, measures and time points

		**0**	**1**		**2**		**3**	
**Method**		**Pre-trial information session**	**Baseline (beginning of day 1 of refresher training)**		**Monthly throughout trial (begins 1-month post-randomisation)**		**End of trial (6 months post randomisation)**	
			**Control**	**Intervention**	**Control**	**Intervention**	**Control**	**Intervention**

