Acceptability of the recruitment and trial processes to Māori clinicians will be assessed by multiple-choice items within a study-specific questionnaire following the pre-trial information session and at the end of the trial. Māori clinicians choosing not to enrol in the trial will also be offered the opportunity to speak kanohi-ki-te-kanohi (face to face) or via phone with a Māori research team member, to discuss their impressions and any concerns about trial recruitment processes and/or methodology that contributed to their decision not to participate, and this qualitative data will be recorded.

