### Statistical considerations

#### Sample size and justification

As this is a feasibility study, sample size calculations are not required, and a formal power calculation is not appropriate, given that the primary outcome for this pilot is feasibility [38]. Instead, sample sizes for feasibility studies should be based on pragmatic considerations [39]. However, for the RCT, it is envisaged that the primary outcome will be *adoption*: clinician self-report of the number of unique families to whom PCIT was delivered in the most recent representative 1-week period at 6 months post-randomisation, compared to baseline. These data will be collected.

Relevant pragmatic considerations included the size of the group of PCIT-trained clinicians thought to be practicing in the Tāmaki Makaurau/Auckland region, excluding the research team (approximately 70). Also, the budget for the research project will only support limited co-worker hours, and the purchase of limited time-out pop-up cubicles and limited audio-visual equipment and toy packages. Given these practical constraints, we hope to recruit 10 participants per condition or 20 overall. We are interested in evaluating whether the proposed recruitment methods will be effective in a future, larger trial. While we will aim to recruit this number, our ability to do so will provide valuable data around our ability to recruit sufficient participants for a fully powered trial using the described methods.

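### Unrestricted allocation could leave no Māori clinician with the arm-specific components, although a stated aim concerns the intervention's acceptability to Māori clinicians

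*Protocol article*

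**What the plan says.** Under Study aims, the protocol article sets out to "determine the acceptability of the reimplementation intervention for Māori participants". This is listed apart from the aim on acceptability to clinicians in general, and the Abstract names cultural responsivity among the things to be assessed.

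Under Intervention, "clinicians allocated to the intervention condition will receive the following": a toy pack, a mobile co-worker, portable audio-visual equipment and a pop-up time-out cubicle. Table 2 marks bookings of the equipment, tents and co-worker for the intervention arm only. Other elements are shared: under All participants, everyone gets the refresher training, and "participants across both groups will be offered optional complimentary weekly 1-h group PCIT-oriented consultation".

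Under Randomisation and blinding strategies, the statistician prepares the sequence "using a simple 1:1 randomisation with no restrictions". All participants are recruited and trained before allocation at the end of the second training day. Table 2 places ethnicity in the baseline survey at the start of the first day.

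Under Sample size and justification, "we hope to recruit 10 participants per condition or 20 overall". The Intervention section says that "a number of PCIT-trained clinicians are Māori (14.8% in our 2021 survey". No target or expected number of Māori participants is given.

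Under Secondary outcomes, the outcome written specifically for Māori clinicians concerns how the trial is run: "Acceptability of the recruitment and trial processes to Māori clinicians will be assessed by multiple-choice items within a study-specific questionnaire". Acceptability of the components is measured for participants generally, by bookings, consultation attendance and ratings in a post-trial interview.

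**The concern.** The aim depends in large part on Māori clinicians who have used the arm-specific components. In a sample of 20 they will be few, and nothing in the allocation ensures that any of those who enrol receive the package. Simple randomisation can place all of them in the control arm even when several have joined. The pilot would then end without a Māori clinician's experience of the co-worker, equipment, cubicle or toys, and part of a named aim would be lost by chance. Some of that loss is avoidable, because the whole cohort is known before anyone is allocated.

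**Working it through.** The plan sets its sample size on practical grounds, without a formula, and states no expected Māori count, so there is no figure of its own to reproduce.

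**Inputs.** 20 participants, 10 per arm (Sample size and justification); simple 1:1 allocation (Randomisation and blinding strategies); 14.8% Māori (Intervention, from the 2021 survey). Applying 14.8% to the enrolees is an assumption. The other shares below are assumed too, to show the range.

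**Expected numbers at 14.8%.** Overall 20 × 0.148 = 2.96. In the intervention arm 10 × 0.148 = 1.48.

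**Chance of none under the planned allocation.** Each enrolee is both Māori and in the intervention arm with probability 0.148 / 2 = 0.074, so the count is Binomial(20, 0.074).
- P(none) = 0.926^20 = 0.215.
- P(at most one) = 0.558.
- If the arm held exactly 10, P(none) = 0.852^10 = 0.202, so the result barely depends on that detail.

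**Chance of none given the number of Māori clinicians enrolled.** Under simple randomisation it is 0.5^m: 25% for m = 2, 12.5% for m = 3, 6.25% for m = 4.

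**With a Māori stratum split as evenly as possible, an odd one at random.** None reach the package only if no Māori clinician enrols, or if exactly one does and goes to control: P(none) = P(0 enrol) + 0.5 × P(1 enrols).
- At 14.8%: 0.852^20 = 0.041, and P(1 enrols) = 20 × 0.148 × 0.852^19 = 0.141. Total 0.041 + 0.071 = 0.111 (unrounded inputs).
- At 25%: 0.75^20 = 0.003, and P(1 enrols) = 20 × 0.25 × 0.75^19 = 0.021. Total 0.003 + 0.011 = 0.014.

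| Māori share among enrolees | Expected in intervention arm | P(none), as planned | P(at most one), as planned | P(none), with stratum |
|---|---|---|---|---|
| 14.8% (survey) | 1.48 | 21.5% | 55.8% | 11.1% |
| 25% (assumed) | 2.5 | 6.9% | 26.7% | 1.4% |

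At other assumed shares, P(none) as planned is 36% at 10%, 12% at 20% and 4% at 30%. Even at 30% only three Māori clinicians would be expected in the arm.

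**What stratifying does and does not do.** At 14.8% it removes 21.5 − 11.1 = 10.4 percentage points. The remaining 11.1 points arise because none or only one may enrol, which an even split cannot cure. The expected number in the arm stays at 1.48.

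**The case against.** A reader might infer that the aim can rest only on Māori clinicians allocated to the package. The documents do not support that. Outcomes and measures says "Some aspects of the re-implementation intervention occur at one point in time (e.g. the refresher training", Table 1 describes both the training and the consultation groups as part of the intervention, and both reach the control arm. So does the discussion, led by a Māori PCIT provider, of culturally responsive delivery. Table 2 marks end-of-trial interviews for both arms, so all the Māori enrolees, about three at the survey share, could comment on the shared elements. The shortfall is exact only for the four arm-specific components and for the package as a whole.

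Nor is acceptability of the intervention to Māori clinicians unmeasured. Secondary outcomes already plans interview ratings of the components, and ethnicity is on file. Only separate reporting is unstated, and that is often left to a fuller document.

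The 21% is not a forecast. The survey share does not describe Auckland enrolees, and Setting and proposed recruitment plans whanaungatanga-based contact and calls by a Māori team member, which may raise it. This stands, and is why a range is shown. Outreach changes who enrols, however, and not who is allocated to the package.

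Finally, a pilot needs no power, the aim is descriptive, and stratifying leaves one or two people as the typical number. All of this is correct. It is a reason to word the aim more modestly, and it does not remove the case for a cheap allocation step that prevents an avoidable zero.

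**Conclusion.** The point holds in a limited form. With simple allocation of 20 clinicians, and if the 14.8% survey share applied, about 1.5 Māori clinicians would be expected to receive the arm-specific components, with about a 21% chance of none. That chance is 7% at an assumed 25% share and 12.5% if exactly three enrol. About half of the 21% is avoidable through allocation; the rest depends on how many enrol.

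It would go too far to say that the aim would be wholly unanswered. The shared elements can be judged in both arms, and a low Māori count would itself inform the part of the same aim that concerns cultural influences on recruitment. Nor is the trial's feasibility verdict at risk: enrolment, completion and the progression criteria do not depend on this aim. The allocation change is the substance of the point. The wording of the aim and the separate reporting are minor and accompany it.

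**What to change.** 1. Allocate Māori clinicians as their own stratum, divided between arms as evenly as their number allows, with an odd one assigned at random. The statistician can do this from the baseline ethnicity data, since enrolment is complete before allocation. At least one Māori clinician is then allocated to the package whenever two or more enrol.
2. In Secondary outcomes, state that the component ratings already planned for the post-trial interview will be reported separately for Māori clinicians in the intervention arm.
3. In Study aims, replace *determine* with *explore* for this aim, and state that one to two Māori clinicians are expected in the intervention arm if the survey share applies.

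The cost is a two-stratum allocation list, a few changes of wording and a more modest stated aim. No extra participants, staff or instruments are needed.
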